#### Inclusion and exclusion criteria

Women aged 18 to 75 years, meeting fibromyalgia criteria as defined by the American College of Rheumatology (2016) (ACR2016), or with a formal diagnosis by a medical practitioner, and willing to comply with study requirements, including travelling to the study site in Auckland, NZ, will be invited to join the study.

Exclusion criteria for both groups include being a current smoker, having a diagnosis of diabetes mellitus, being pregnant or breastfeeding, having any major comorbid illness (e.g., malignancy, active inflammatory or metabolic disease), or being unable to withhold anti-inflammatory medication for at least 48 hours. At least 4 weeks must lapse after any antibiotic treatment before enrolment.

Healthy controls must meet the same criteria, except they must *not* meet criteria for fibromyalgia.

#### Recruitment

A study website has been designed to enhance the recruitment phase of this study. The site contains information about the project, details on the study design, and a link to the eligibility survey, hosted on REDCap. Links to this website, along with summary information, will be provided to a range of health professionals thought to have interactions with people with fibromyalgia. Printed flyers will be distributed to medical centres, allied health clinics and pharmacies, and displayed on community and library noticeboards within a 5km radius of the study site. As each participant completes submission of study samples, a report detailing the available results will be sent to them and their medical practitioner. A brief outline of the study will be included, along with a recruitment flyer.

In addition, the study will be promoted via advertisements and social media posts via support groups and community pages, including the Facebook page of Fibromyalgia NZ.

Volunteers with fibromyalgia will be requested to invite a healthy adult female who is a family member (sister, daughter, mother), household cohabitant or close friend to participate to form our control group. Where numbers for controls are lacking, age-matched controls will be sought via social and professional networks.

In lieu of financial compensation to volunteers, each participant will receive a report detailing results from tests analysed at the study site. Together these have a retail value of more than NZ$500.

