## Objectives

The primary aim of this clinical study is to investigate the relationships between the composition and function of the oral and gastrointestinal microbiota, digestive symptoms, and clinical presentation of adult women living with fibromyalgia and compare these to age or family-matched healthy female controls.

The specific aims are to assess and contrast: (A) the interaction between the oral and faecal microbiome, including its function, complexity, and diversity, and (i) digestive symptoms; (ii) symptoms associated with fibromyalgia; (iii) human gene expression, and (B) the interaction between digestive symptoms and symptoms associated with fibromyalgia. We will also examine these factors in relationship to the human transcriptome.

Factors known to influence the composition of the gut microbiome, including oral health, diet, sleep, body composition, medication and supplement use will be evaluated. We will also evaluate redox balance, glycaemic control, and environmental mould exposure.

The study is designed to test the hypothesis that the gut microbiome, and its transcriptome, is associated with digestive function, and the symptoms associated with fibromyalgia.

Here we detail the study protocol, recruitment strategy and analytical procedures.

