### Participants and recruitment

This is a prospective, single-centre, cross-sectional case-controlled, observational study. We aim to recruit at least 100 adult women meeting fibromyalgia diagnostic criteria and a minimum of 50 matched controls. Limiting the study to females reduces the confounding influence of gender difference on gastrointestinal function and the gut microbiome. To determine suitability for inclusion as a participant or as a healthy control, initial screening will be conducted via a survey hosted on Research Electronic Data Capture (REDCap) (via the University of Sydney). Prospective volunteers will then be contacted directly by the study co-ordinator to confirm suitability and book appointments as appropriate.

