#### Sample size

Based on 2002 data, the estimated prevalence of fibromyalgia in the NZ population (~5 million) is 1.5% [23]. Up to 98% of women with fibromyalgia may have at least one FGID [24], thus for alpha of 0.05 and confidence interval (CI) of 95%, no less than 55 participants and 55 controls are required.

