### Environmental samples

To determine interactions with mould exposure in the home (and/or workplace), participants will be asked to take surface swabs from six unique sites in their indoor environment where mould is visible, or typically grows. A list of likely places will be provided. After collecting a sample with a sterile flocked swab (Hydraflock, 25-3206-H, Puritan Medical Products, Guildford, ME), the swab tip is snapped into a pre-labelled tube containing RPB. The site of sample collection is matched to the tube identifier on a logging sheet, including a description of the sample and site collected from.

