### Statistical analysis

All data will be anonymised and saved in password protected computer hosted on the University of Sydney’s Data Management System. Statistical analysis will be performed using specialist software. The level of significance will be set at *p* < 0.05.

Descriptive statistics will be used to detail the characteristics of the cohort, and the students’ t-test will be employed to compare participants and controls. Anthropometrics, symptom prevalence, scores and co-morbidities will be compared using univariate and multivariate analysis of variance, as appropriate.

After clustering data according to conventions appropriate to each of the questionnaires in the participant survey, group differences will be assessed using students’ t-tests, Wilcoxon signed-rank test chi-squared tests, and logistic regression, as appropriate.

For microbiome analyses, after stratification by age-groups to allow for variances that may be associated with reproductive life-stages, correction for multiple comparisons (e.g., using Benjamini–Hochberg FDR) and normalised operational taxonomy units will be evaluated using Pearson's correlations. Strength of associations with clinical variables will be tested using Spearman's Rho. Further statistical analysis of the data will be performed using machine learning methods.

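### Controls are mostly nominated by the cases and called matched, but the named group comparisons carry no pair or household link, which costs precision and weakens any home-mould contrast for cohabiting pairs

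*Protocol article*

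**What the plan says.** Under Recruitment, each woman with fibromyalgia is asked to "invite a healthy adult female who is a family member (sister, daughter, mother), household cohabitant or close friend", and these women form the control group. Unlinked controls are a fallback: "Where numbers for controls are lacking, age-matched controls will be sought via social and professional networks".

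The Objectives describe the design as a plan to "compare these to age or family-matched healthy female controls". Participants and recruitment sets the target at "at least 100 adult women meeting fibromyalgia diagnostic criteria and a minimum of 50 matched controls", while Sample size gives "no less than 55 participants and 55 controls are required".

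In Statistical analysis, the Student's "t-test will be employed to compare participants and controls". Anthropometrics, symptom scores and comorbidities go to univariate or multivariate analysis of variance. Questionnaire group differences go to t-tests, the Wilcoxon signed-rank test, chi-squared tests and logistic regression, as appropriate. Microbiome analyses are stratified by age group because of reproductive life-stage, and correlations with clinical variables follow. The section mentions neither a matched set nor a household.

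Under Environmental samples, "participants will be asked to take surface swabs from six unique sites in their indoor environment". Home and/or workplace may be sampled.

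**The concern.** A woman and the relative, housemate or friend she brings are likely to resemble each other in diet, microbiome and environment, and relatives also share genes. The design calls this matching, but the named analysis mostly ignores it. Four things follow.

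- **Group comparisons.** An unpaired test uses too large a standard error when pairs are positively correlated. The precision that matching could buy is lost.
- **Pooled associations.** If microbiome-symptom correlations are run across cases and controls together, linked women count as independent and the variance is understated.
- **Age.** A control may qualify through family or through age. Mothers and daughters qualify through family, so family matching does not ensure similar age. The plan itself treats age as important enough to stratify on, and such pairs can fall into different strata.
- **Mould.** When a control lives with her case, both may swab the same home, and the contrast within that pair is reduced, possibly to nothing.

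The link between a case and her control is easy to record at enrolment and hard to reconstruct later.

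**Working it through.** **Inputs.** From the article: 100 cases and 50 controls (Participants and recruitment), 55 and 55 (Sample size), significance at 0.05. Assumed, because the article does not give them: unit SD; within-pair correlation ρ = 0.3, range 0.1 to 0.5; every control linked to one case (relaxed in step 5); the mould rates and cohabiting shares in step 7. Tests are two-sided with normal approximations.

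**1. The plan's own figure.** The 55 per group cannot be reproduced from the stated inputs, because no control rate, power or margin is given. A 95% interval around 98% yields 55 only with a half-width of about 3.7 points: 1.96² × 0.98 × 0.02 / 0.037² = 55. Nothing stated there uses pairing, so it does not show which analysis was intended.

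**2. Unpaired difference in means, 100:50.**
- Variance the test assumes: 1/100 + 1/50 = 0.030.
- Actual variance with m linked pairs: 0.030 − 2mρ/(100 × 50). With m = 50 this is 0.030 − 0.02ρ.
- At ρ = 0.3: 0.024. The standard error is √(0.030/0.024) = 1.12 times too large.
- Actual type I error: 2 × [1 − Φ(1.96 × 1.118)] = 2.8%.

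**3. A model that uses the link.** For 50 pairs plus 50 unlinked cases, put k = 50/(1 − ρ²). The information matrix for the two group means has diagonal entries k + 50 and k, and off-diagonal −ρk. At ρ = 0.3, k = 54.95, and the variance of the difference is (104.95 + 54.95 − 2 × 16.48)/(104.95 × 54.95 − 16.48²) = 0.0231.

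**4. Detectable difference at 80% power**, in SD. The first column is (1.96 + 0.842) × √0.030. The second is what the unpaired test really achieves, 1.96√0.030 + 0.842√(actual variance). The third is 2.802 × √(model variance).

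| ρ | Assumed by unpaired test | Achieved by unpaired test | Matched-set model | Actual type I error |
|---|---|---|---|---|
| 0.1 | 0.485 | 0.480 | 0.468 | 4.2% |
| 0.3 | 0.485 | 0.470 | 0.426 | 2.8% |
| 0.5 | 0.485 | 0.458 | 0.371 | 1.6% |

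At ρ = 0.3 most of the gain comes from the correct standard error: 0.024 against 0.030, then 0.0231 from better weighting. At a true difference of 0.5 SD, power for the difference in means is 85% with the unpaired standard error and 90% with the correct one.

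**5. Other configurations, ρ = 0.3.**
- 100:50 with 25 controls linked: actual variance 0.030 − 0.003 = 0.027, type I error 3.9%.
- 55:55 fully paired: assumed 2/55 = 0.0364, actual 0.7 × 0.0364 = 0.0255, type I error 1.9%; power at 0.5 SD is 79% against 88%.
- Paired test on the 50 pairs only, dropping 50 cases: variance 2 × 0.7/50 = 0.028, power 85% at 0.5 SD. That is no better than the unpaired test.

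**6. Pooled analyses.** With 50 pairs and 50 unlinked cases, the variance of a pooled mean is inflated by (150 + 100ρ)/150: 1.07, 1.20 and 1.33 at ρ = 0.1, 0.3 and 0.5. For a correlation between two unrelated variables, ρ is replaced by the product of their two within-pair correlations, so the inflation is smaller: about 1 + 100 × 0.09/150 = 1.06 when both are 0.3, and 1 + 100 × 0.25/150 = 1.17 when both are 0.5.

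**7. Mould, illustration only.** Take true rates of 50% in cases and 25% in non-cohabiting controls. Let a share c of controls live with their case and carry the case rate, the extreme of full sharing. The control rate becomes 0.5c + 0.25(1 − c), and the difference shrinks to 0.25(1 − c). Two-proportion power at 100:50 is 85% at c = 0, 76% at c = 0.10, 59% at c = 0.25 and 30% at c = 0.50.

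**The case against.** The strongest reply is that the article never says the women are analysed as independent. It lists a paired test, a t-test can be paired, and the list is qualified by appropriateness. This is a condensed article, and model details may sit in an analysis plan that is not shown. A reader might infer that the whole analysis is unpaired, and the text does not support that. It mixes paired and unpaired methods without saying which applies to nominated controls. What remains is that the article names its tests, most do not fit the matched design it describes, and the signed-rank test cannot use a 100:50 sample in full.

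Second, the error in the group comparison is conservative. It produces no excess of false positives, and it shrinks as more fallback controls enter. That is correct.

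Third, a reader might infer that the groups differ in age. That is not shown: mothers are older than their case, daughters younger, and sisters or friends may be close in age. Only the weaker statement holds, that family matching does not secure similar age.

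Fourth, a reader might infer that the mould comparison is between women in the same home and that its contrast is zero. The documents do not support this. Relatives and friends may live elsewhere, fallback controls need not share a home, workplace swabs are allowed, and two housemates may choose different sites. No case-control mould test is written out; mould is one of several further factors to be evaluated.

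**Conclusion.** The point holds in a limited form. The design links most controls to a case, the article calls them matched, and the named methods neither carry that link nor say which comparisons are paired. For the group comparison this is a loss of precision, not a source of false positives: the detectable difference could come down to about 0.43 SD (0.47 to 0.37), and the nominal 5% test runs at about 2.8% (4.2% to 1.6%). These figures assume ρ of 0.3 (0.1 to 0.5) and all 50 controls linked one-to-one; with half linked the effect is roughly half as large. Correlations that pool the groups would understate their variance, by an amount that depends on the within-pair correlation of both variables. The article does not say whether its correlations pool the groups. The loss of home-mould contrast is confined to cohabiting pairs and ranges from none to total, since their share is unknown. The plan should be changed on this point, but the study does not fail on it.

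**What to change.** 1. At enrolment, record a matched-set identifier, the relationship (relative, cohabitant, friend, unrelated age-matched) and whether the control shares a home with her case.
2. Replace the unpaired group tests by linear mixed models with a matched-set random intercept for continuous outcomes, and by GEE or mixed logistic models for binary ones, with age as a covariate. These keep unlinked cases and fallback controls.
3. Reserve signed-rank or conditional logistic methods for linked pairs, and say so. Conditional logistic regression drops every case without a linked control.
4. Apply the same clustering to any association that pools cases and controls.
5. Base any case-control mould comparison on non-cohabiting controls, and repeat the microbiome comparison without cohabitants as a sensitivity analysis.

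The cost is small: a short addition to the enrolment form, slightly more complex models, and fewer controls in the mould comparison.

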## Study procedures

The FIDGIT Study will be conducted at House of Health in Auckland, NZ, with recruitment commencing November 2021, under supervision of the University of Sydney. All eligible volunteers will be required to attend the study site on at least one, and on up to 4 occasions.

At the initial visit, after satisfying any questions and obtaining informed consent, a unique participant identifier will be allocated. A trained technician will perform baseline assessments and phlebotomy. Details of current medication and supplement use will be documented, and procedures for at-home sample collection outlined and equipment provided. To augment the verbal and written information, some at-home tests will have additional animated instructions published on YouTube (see Declarations).

At the first visit, participants will proceed to a hydrogen-methane breath test, as detailed under *Breath Testing*. While undertaking breath testing, the comprehensive integrated questionnaire and the dietary assessment tool are completed.

## Clinical measurements

All volunteers will attend the enrolment appointment after fasting for a minimum of 12 hours (water only), having withheld dietary supplements and anti-inflammatory medication for at least 48 hours, and before taking any morning medications. After screening for risk of recent exposure to, or symptoms of, SARS-CoV2 infection, including heart rate, peripheral oxygen saturation, and temperature, volunteers will be weighed without shoes on an electronic scale and documented to the nearest 0.1kg. Height will be measured to the nearest 0.5 cm using a wall-mounted stadiometer. These data are used to calculate body mass index (BMI) using the formula: body weight (kg)/height^2^ (m). Systolic and diastolic blood pressure will be measured (while seated) by the study co-ordinator (a registered nurse) with a manual sphygmomanometer on the arm not used for venepuncture.

## Medication and dietary supplements

Prospective participants are asked to list their current medications and dietary supplements when completing the eligibility survey. This will aid identification of conditions that trigger an exclusion flag and aid the study co-ordinator’s instructions to participants regarding medication and the required fasting and exclusion period. The list of medications and supplements will be verified at the initial appointment, with determination of duration of use. These are then catalogued in an Excel® spreadsheet; medications according to the ATC/DDD drug classification system [25], to the second level, or the third level for gastrointestinal system-specific drugs. Supplements will be coded according to the Australian Health Survey (AHS) dietary supplement 5-digit classification code [26].

## Sample collection & analysis

### Blood samples

At the initial visit - while fasting - venous blood samples will be collected using a McKesson Prevent® safety winged blood collection set (McKesson MFR# 2194) with BD Vacutainer® one-use holder (Becton Dickinson 64815), into 1x lithium heparin and 1x EDTA BD Vacutainer®. After identifying a suitable vein, and the site cleaned using an 70% isopropyl alcohol swab, a tourniquet will be applied briefly until venepuncture is achieved. Prolonged venous occlusion is to be avoided. All the following preparatory steps are to be completed within 5 minutes of the blood draw.

Analysis of frozen samples will be done as a batch after completion of recruitment.

#### RNA Transcriptomics

Within 2 minutes, using a Rainin Pipet-Lite L-1000 XLS pipette (Mettler Toledo), with 1000μl pipette tip (ART® BioProducts), an aliquot of 500μL of blood will be transferred from the EDTA vacutainer into a 5mL tube containing 2mL of a proprietary RNA Preservative Buffer (RBP, Viome Life Science, USA), capped and shaken vigorously for 30 seconds. After labelling, this is then stored at -20°C until transfer to a -80°C freezer.

With a new pipette tip, blood from the same EDTA tube is dripped to fill 4 circles on Whatman® protein saver cards (Sigma WHA10534612). After labelling and being allowed to dry at room temperature for 30 min, they are then placed in individual zip-lock bags with two 5g sachets of silica gel moisture absorbent (S-3905), sealed and stored at -20°C until transfer to a -80°C freezer.

#### Blood chemistry

From the lithium heparin vacutainer, 100μL of blood is transferred using Rainin Pipet-Lite L-300 XLS pipette (Mettler Toledo), fitted with a Rainin 300μL BioClean Ultra LTS pipette tip (Mettler Toledo), into the entry port on a fresh MetLac12 reagent disc (Abaxis®, USA, 400-1037) and immediately inserted into a Piccolo Xpress® analyser (Abaxis®) for basic blood chemistry (glucose, sodium, potassium, chloride, total carbon dioxide (CO_2_), calcium, phosphorus, magnesium, blood urea nitrogen, lactate, albumin, and creatinine).

The analyser is designed for point of care analysis of blood samples. Each single-use disc contains a diluent, which is automatically mixed with the blood sample, and using centrifugal and capillary forces into separated cuvettes, which contain the reagent beads specific for each analyte. Reaction products in the cuvettes are then measured photometrically. The equipment has inbuilt self-calibration and quality control functions, which are automatically done with each sample analysed.

#### Redox status

Finally, two separate blood samples (20µl and 50µl) will be collected from a capillary finger prick for evaluation of free oxygen radicals (FORT) and free oxygen radical defenses (FORD) according to the manufacturer’s instructions [27].

The FORT/FORD test is a reliable measure of whole blood oxidative stress [28]. It is a colorimetric assay, using disposables purchased as commercially available kits (BioMed Science/ Callegari Sr, Italy). The filled capillary tubes are immediately added to a 2mL tube with supplied reagents, centrifuged (CR6000), and analysed in the automated dedicated spectrophotometer (CR3000 RCH, FormPlus, Callegari, Parma, Italy).

FORT is an indirect measure of reactive by-products in whole blood. It is based on Fenton’s reaction, determining the capacity of transition metal ions (Fe^3+^ /Fe^2+^) to catalyse the breakdown of hydroperoxides (R-OOH) into derivative radicals [alkoxyl (R-O•) and peroxyl radicals (R-OO•)]. FORT units are expressed as equivalent concentrations of H_2_O_2_ mmol/L^-^1, with one FORT unit corresponding to approximately 7.6 mmol/L of H_2_O_2_ (equivalent to 0.26 mg/L) [27].

FORD is an indirect measure of the antioxidant capacity in whole blood. It is based on the capacity of ascorbic acid, glutathione, and albumin in the sample to reduce a preformed radical cation. FORD is expressed as mmol/l of Trolox (6-hydroxy-2,5,7,8-tetramethylchroman-2-carboxylic acid; a water-soluble analogue of vitamin E) [27].

### Stool

Participants will be asked to collect faecal samples as soon as practicable after the initial visit, while abstaining from probiotics and antibiotics. After first urinating, EasySampler® stool collector paper (GP Medical Devices, Holstebro, Denmark) is used to prepare a stool-catch platform. From the deposited stool, a pea-sized scoop will be taken with the provided scoop-spoon and immediately transferred to a pre-labelled stool tube (Sarstedt NC9574115, Fisher Scientific, Waltham, MA), containing 6 mL RNA preservative buffer (RPB) and 9-13 beads that facilitate mixing of the sample. After vigorously shaking the tube for 30 seconds, a 30-second rest period is followed by repeat shaking/resting two more times**.** This tube is then placed inside a white-capped stool tube (Sarstedt, Fisher Scientific NC1933356; Waltham, MA) containing an absorbent liner, then into a zip-lock bag and frozen at -20°C until transfer to -80°C freezer.

